### Study outcomes

The primary outcome of this study is the incidence of clinically relevant pDDIs per 1000 medication administrations. To be able to compare our results to other studies, we also defined secondary outcomes. These are the number of pDDIs per patient, the number of clinically relevant pDDIs per patient, the proportion of patients admitted to the ICU with at least one pDDI, and the proportion with at least one clinically relevant pDDI [9]. Other secondary outcomes are ICU length of stay, the override rate of clinically relevant pDDI alerts and the number of ADEs related to DDIs per 1000 medication administrations. In Table 1 definitions of study outcomes are described. These definitions are in line with previous studies [5, 8].

**Table 1 Tab1:** Overview of study outcomes

Study outcomes	Definition
pDDI	Two potentially interacting medications administered concomitantly which could result in an actual DDI.
Clinically relevant pDDI	A pDDI considered clinically relevant for the ICU setting, according to the results from our Delphi procedure.
ADE related to DDI	A DDI that resulted in patient harm.
Appropriately handled pDDI	Two potentially interacting medications were administered concomitantly (pDDI), but there is evidence that adequate measures were taken to prevent patient harm or diminish the risk of patient harm.

In addition, we will also measure the proportion of appropriately handled clinically relevant pDDIs. This is an important outcome, specifically in the ICU setting, where the patient is in a critical condition and sometimes the risk of prescribing interacting medications is subject to the need for treatment [17]. Furthermore, if prescribing a pDDI cannot be averted, there are several management strategies to keep the potential harm to a minimum. Management strategies include for example monitoring laboratory values such as creatinine, potassium, therapeutic drug monitoring and adjustment of medication dosage [8]. Because of this, it is not only important to know whether a reduction in the number of clinically relevant pDDIs has occurred, it is also important to know how many pDDIs occurred that were handled appropriately, for example by conducting therapeutic drug monitoring.

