To assess whether a clinically relevant pDDI alert is handled appropriately or not, for each clinically relevant pDDI we will list the possible management strategies based on the recommendations available in the G-standard. A pDDI will be considered as handled appropriately if there is ‘evidence in the data’ that one or more of the defined management strategies has been implemented based on medication, laboratory and ECG data of the patient.

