### Data collection

To assess the effect of our intervention on the primary and secondary outcomes, and to gain insight in pDDI type and occurrence for the purposes of our Delphi procedure, we will use routinely recorded data extracted from MetaVision ICU, MiM/MiM+, and the NICE registry.

Data covering all ICU admissions in the period from at least one month prior to the MIM+ implementation up to one month after the intervention period will be extracted. All data from Metavision ICU and MiM/MiM+ will be collected at the patient level using a coded admission number of the patient as an identifier. This coded admission number cannot be used to identify a specific patient. The following routinely recorded data from Metavision ICU will be extracted: medication orders, orders for an electrocardiogram (ECG) and laboratory orders. Medication orders will include the name of the ordered medication, generic product code of the medication, dosage and frequency, validation of the order indicating whether the medication order was actually administered, the start and end time of the order, and whether or not the order was cancelled. In MetaVision ICU, each administration is registered separately. These data are necessary to assess the primary outcome: the occurrence of clinically relevant pDDIs per 1000 medication administrations. Laboratory orders will include name of test ordered, date and time of the order, and for results of the test. ECG orders will include date and time of the order. ECG and laboratory data together with medication data are necessary to assess if, following a pDDI alert, appropriate management strategies were employed (secondary outcome: appropriately handled clinically relevant pDDIs) and to assess whether ADEs occurred (secondary outcome: number of ADEs related to DDIs per 1000 medication administrations).

The following routinely recorded data from MiM and subsequently MiM+ will be extracted: all (clinically relevant) pDDI alerts that were produced, date and time of the alert, which medication (name and generic product code) was involved, if the alert was overridden or not, and if entered by the user, the reason for overriding the alert. These data are necessary to assess the secondary outcome: override rate of (clinically relevant) pDDI alerts per 1000 medication administrations.

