To detect (clinically relevant) pDDIs in the medication orders data, we will develop a computerized algorithm based on the pDDI rules from the G-standard. This algorithm will then be applied to medication order data from the participating ICUs. Only validated medication orders, i.e. medication orders that were actually administered, will be considered. In addition, each separate administration for a specific drug will be attributed to one composite medication administration if the time gap between separate administrations does not exceed a specific amount of time, such as 24 h (regardless of the route of administration).

A second developer will validate the algorithm. To assess the number of ADEs related to DDIs per 1000 medication administrations, we will develop computerized ADE triggers. Triggers are sentinel words or events that may point to the occurrence of an ADE, such as increased or decreased laboratory values, ordering an ECG or prescribing an antidote [31]. The triggers that we develop and ADEs identified by these triggers will be published along with the results of this study.

In addition to data from Metavision ICU and MiM/MiM+, we will also use data submitted to the NICE registry by the participating ICUs. These data include clinical, physiological and demographic data required to calculate outcomes such as ICU length of stay, hospital length of stay, hospital mortality, and expected mortality based on disease severity predicted from clinical data of the first 24 h of ICU admission [27]. Data from Metavision ICU, MiM/MiM+ can be linked with NICE registry data using the earlier mentioned unique coded admission number.

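### An ECG order can count both as appropriate handling and as an ADE trigger, so alert-prompted ECGs can bias the ADE outcome upward under MiM+

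*Protocol article*

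**What the plan says.** Two secondary outcomes draw on the same medication, laboratory and ECG data.

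- **Appropriate handling** (Protocol article, Study outcomes). A clinically relevant pDDI is credited when the record shows that "one or more of the defined management strategies has been implemented based on medication, laboratory and ECG data of the patient". The examples given are "Management strategies include for example monitoring laboratory values such as creatinine, potassium, therapeutic drug monitoring and adjustment of medication dosage". ECG is not among these examples, but ECG data are named in the rule itself and again in Data collection.
- **ADEs related to DDIs per 1000 medication administrations.** Table 1 defines the event as "A DDI that resulted in patient harm". Data collection says that computerized triggers will be developed to find it: "Triggers are sentinel words or events that may point to the occurrence of an ADE", with the examples "such as increased or decreased laboratory values, ordering an ECG or prescribing an antidote". It adds: "The triggers that we develop and ADEs identified by these triggers will be published along with the results of this study". No step from a fired trigger to confirmed harm is described.

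On what will be extracted, Data collection states: "ECG orders will include date and time of the order". No ECG result is listed. For laboratory orders, the test result is listed as well as the order.

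**The concern.** An ECG ordered after a pDDI is favourable evidence in one outcome and unfavourable evidence in the other, and no rule assigns it to one role. The listed ECG data cannot settle the matter afterwards, because a precautionary ECG and one ordered for a suspected arrhythmia leave the same record.

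This would be mere noise if ECG ordering were unrelated to the study condition, but the intervention acts on that behaviour. Under Establishing clinically relevant pDDIs, a pDDI is relevant if it should always be avoided or if it calls for monitoring beyond the standard. An alert for the second kind does its job when it prompts monitoring. Ascertainment of ADEs can therefore depend on the condition.

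At stake is the only listed outcome that directly measures harm from interactions. An upward bias under MiM+ could turn a true reduction into an apparent null result or an apparent increase.

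**Working it through.** The plan gives no ADE rate, no ECG ordering rate and no predictive value for a trigger, so there is no stated figure to reproduce. The check has two parts.

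**1. The definitions side by side**

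| Event after a pDDI | Can credit handling? | Example ADE trigger? | Can the listed data separate the roles? |
|---|---|---|---|
| ECG ordered | Yes, ECG data are named | Yes, the order itself | No, only date and time |
| Laboratory test, normal result | Yes | No | Yes, result listed |
| Laboratory test, abnormal result | Yes | Yes, the value | Partly: the value is known, the reason for testing is not |

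The direct overlap is confined to the ECG order. For laboratory data the remaining route is indirect: more testing finds more abnormal values.

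**2. An illustration of size; apart from the 20% reduction, every input is an assumption**

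Counted ADEs per pDDI = h + (1 − h) × e × q, where

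- h is the true harm rate per pDDI, the same in both conditions (2% to 10%), with every true harm counted;
- e is the share of pDDIs followed by an ECG order, doubling from 10% to 20% or from 20% to 40%;
- q is the probability that an ECG order without harm is counted as an ADE.

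The last column multiplies by 33.6 / 42.0 = 0.80, the fall in clinically relevant pDDIs assumed under Sample size. It supposes that true ADEs fall in proportion and that the number of administrations is stable. The rows with q of 1 or 0.25 show the extremes.

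| h | e | q | Control | MiM+ | Ratio | Ratio × 0.80 |
|---|---|---|---|---|---|---|
| 10% | 10% to 20% | 1 | 0.10 + 0.90 × 0.10 = 0.190 | 0.10 + 0.90 × 0.20 = 0.280 | 1.47 | 1.18 |
| 2% | 20% to 40% | 1 | 0.02 + 0.98 × 0.20 = 0.216 | 0.02 + 0.98 × 0.40 = 0.412 | 1.91 | 1.53 |
| 10% | 10% to 20% | 0.25 | 0.10 + 0.90 × 0.10 × 0.25 = 0.1225 | 0.10 + 0.90 × 0.20 × 0.25 = 0.145 | 1.18 | 0.95 |
| 2% | 20% to 40% | 0.25 | 0.02 + 0.98 × 0.20 × 0.25 = 0.069 | 0.02 + 0.98 × 0.40 × 0.25 = 0.118 | 1.71 | 1.37 |
| any | any | 0 | h | h | 1.00 | 0.80 |

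A smaller rise in ordering, from 20% to 25%, multiplies ECG-triggered events alone by 25 / 20 = 1.25. With 20% fewer pDDIs this gives 0.80 × 1.25 = 1.00: no visible rise, but a true 20% reduction hidden.

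For laboratory triggers, if the share of pDDIs tested rises from 50% to 70%, detected abnormal values rise by 70 / 50 = 1.40. If testing is near-routine and rises from 95% to 99%, they rise by 99 / 95 = 1.04.

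**The case against.** The strongest reply is that a trigger is not an ADE. The text says only that triggers may point to one, Table 1 requires harm, and triggers and the ADEs found through them are named separately. The list is introduced as examples, the trial's own triggers are still to be developed, and nothing says that an ECG order will be both strategy and trigger for the same pDDI. A condensed article may leave confirmation and timing rules to a fuller document. This stands as far as it goes: with full confirmation (q = 0) the bias disappears. But the article names the act of ordering an ECG as a trigger and lists no ECG result against which such a trigger could be confirmed.

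The direction is also uncertain. In five of the nine ICUs the intervention suppresses alerts. Monitoring of relevant pDDIs would rise there only if the hypothesis under Theoretical foundation holds and the remaining alerts get more attention. Fewer pDDIs would pull the rate down. Both points stand.

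A reader might infer more: that laboratory tests are triggers in the same way as ECG orders, that the ADE rate must rise under MiM+, or that the two outcomes contradict each other by construction. The documents do not support this. Abnormal values, not test orders, are the laboratory triggers, and results are extracted. A certain rise would need unconfirmed ECG orders to be counted and ordering to increase by more than the fall in pDDIs offsets; neither is stated.

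**Conclusion.** The concern holds for ECG orders. As written, the same order can serve both outcomes, and the listed data cannot tell its two roles apart. Alert-prompted ECGs can therefore bias the ADE outcome upward under MiM+, most plausibly in the four ICUs where pDDI alerts are new, and can mask a benefit even where the measured rate does not rise. For laboratory data only an indirect detection bias remains, small where testing is already near-routine.

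The size is unknown. Across the assumed inputs, a true ratio of 0.80 would be measured as 1.18 to 1.53 if every ECG order without harm counted, and as 0.95 to 1.37 if a quarter did. These ranges show what is possible and do not estimate the trial's bias.

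The point concerns one secondary outcome. The primary outcome counts clinically relevant pDDIs without using triggers, so it and the stated power are unaffected.

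**What to change.** Before the trigger algorithm is written:

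1. Do not let an ECG order, or any other order listed as a management strategy for a pDDI, serve on its own as the ADE trigger for that pDDI.
2. Count an ADE only with evidence of harm in the extracted data, for example an abnormal laboratory result or an antidote, in line with Table 1.
3. Report ECG and laboratory testing rates by condition next to the ADE result, so that a reader can judge any remaining detection bias.

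Restricting laboratory triggers to routine tests is not advised: no reason for testing is among the listed data, so routine tests cannot be identified directly.

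The cost is a rule in an algorithm still to be built, plus one descriptive table; no new data are needed. The downside is that ADEs visible only on ECG go uncounted, but they cannot be verified from the listed data in any case. Claims about ADEs should say so.

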### Data validation

All extracted data will be validated. Validation consists of automated checking for missing values and outliers. Missing values will be reported in the results. Outliers will be investigated and in case of obviously incorrect measurement or entry mistake, outliers will be dropped. Only data that can be linked to the NICE database will be included in the analysis, but in essence every admission in any of the participating ICUs should correspond to an admission in the NICE registry.

### Sample size

To calculate power of our stepped-wedge trial, the statistical software PASS 15.0.4 (NCSS LLC., Kaysville, UT) was used. The calculation considers the following factors: the number of steps, the size of the steps, the number of clusters per step, the number of medication administrations per cluster per step, the anticipated improvement of the intervention, the estimated event rate, and the estimated intra-cluster correlation (ICC).

The anticipated improvement was defined as the overall difference in the number of clinically relevant pDDIs per 1000 medication administrations before and after the MiM+ implementation. We estimate an average relative reduction of 20% in all participating ICUs. According to a systematic review assessing effects of IT-based interventions on outcomes related to DDIs, relative reductions ranging from 15 to 29% have been reported [9].

Based on preliminary analysis of medication data extracted from 5 out of the 9 participating ICUs and one ICU that does not participate in the MiM+ component of the intervention, the number of clinically relevant pDDIs per 1000 medication administrations was estimated to be 42.0 (event rate). With a relative reduction of 20%, the event rate after the intervention is therefore estimated to be 33.6. As an indicator of face validity, a senior intensivist who is involved in the study, considered that a 20% relative reduction from 42.0 is clinically relevant. With a sample of 9 clusters in a stepped-wedge cluster-randomized design with 10 time periods, 9 steps, and one cluster switching from control to intervention at each step and an average number of 6000 medication administrations per cluster, with an average of 600 medication administrations per cluster per time period, calculations show 83% power to detect a relative reduction of 20%, considering an estimated intra-cluster correlation of 0.12. The calculations are based on the Poisson distribution, the test statistic used is the two-sided Wald Z-Test and the significance level of the test is 0.05.

### Statistical analysis

Depending on the distribution of variables, descriptive statistics will be presented as mean and standard deviation, median and IQRs, or percentage as appropriate. Continuous variables will be compared using the t-test or Mann-Whitney test. Categorical variables will be compared with a Chi squared test or Fisher’s exact test. To assess the effect of tailoring pDDI alerts to the ICU setting on the number of pDDIs per 1000 medication administrations we will analyse data from the stepped-wedge trial, adjusting for data clustering and for temporal trends if necessary. A generalized linear model will be fitted with correction for clustering via generalized estimating equations. To adjust for possible confounding patient characteristics (age and disease severity) and other variables (such as the previous use of MiM prior to MiM+) will be considered for addition in the model as covariates. We anticipate that most DDIs will occur around the third day of admission, because by that time chronic home medication often is restarted in the ICU while medication typically prescribed in the ICU is still prescribed [32].

All analyses will be performed according to the intention-to-treat principle. For hypothesis testing a probability level of less than 0.05 will be considered statistically significant. All statistical tests will be two-sided. The R statistical software environment will be used for the analyses.

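### The only tests named for comparing variables other than the pDDI rate ignore ICU and calendar month, and the plan does not confine them to describing the sample

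*Protocol article*

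**What the plan says.** The Statistical analysis section of the protocol article opens with description: "descriptive statistics will be presented as mean and standard deviation, median and IQRs, or percentage as appropriate". Two sentences on testing follow at once. The first reads "Continuous variables will be compared using the t-test or Mann-Whitney test" and the second reads "Categorical variables will be compared with a Chi squared test or Fisher’s exact test". Neither names a variable, an outcome or the groups to be compared.

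The section then turns to the intervention effect, for one measure: "on the number of pDDIs per 1000 medication administrations we will analyse data from the stepped-wedge trial". The adjustment planned for that analysis is described as "adjusting for data clustering and for temporal trends if necessary". The model for it is also named: "A generalized linear model will be fitted with correction for clustering via generalized estimating equations". No other outcome is linked to this model.

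The Study outcomes section lists the secondary outcomes. They are per-patient counts of all pDDIs and of the relevant ones; two patient-level measures, given as "the proportion of patients admitted to the ICU with at least one pDDI, and the proportion with at least one clinically relevant pDDI"; and then length of stay in the ICU, the override rate, and adverse drug events related to interactions. The section adds the share of clinically relevant pDDIs that were handled appropriately. No analysis method is named for any of these. A two-sided 0.05 threshold applies to all hypothesis testing.

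**The concern.** Read literally, the per-patient counts, the patient proportions, length of stay and the handling proportion are continuous or categorical variables, and the four simple tests are the only methods offered for them. Those tests assume independent observations.

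In this stepped wedge, control and MiM+ patients come from different mixes of ICUs and months. The first ICU to switch supplies one control month and nine MiM+ months, and the last supplies nine and one. A pooled test therefore takes part of the difference between ICUs, and any drift over the ten months, for an effect of MiM+.

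The secondary outcomes matter here. They are the protocol's link to other studies, and the override rate bears directly on its alert-fatigue hypothesis.

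**Working it through.** **Layout check against the plan's own figure.** The Sample size section gives 9 ICUs, 10 periods, one ICU switching per step, 600 administrations per ICU-month, 42.0 versus 33.6 per 1000, ICC 0.12 and 83% power. I used the standard stepped-wedge variance with fixed period effects and a random ICU intercept:

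Var = I·s²(s² + T·t²) / [(I·U − W)s² + (U² + I·T·U − T·W − I·V)t²]

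- I = 9, T = 10, U = 45 MiM+ ICU-months, and W = V = 285 (sums of squared column and row totals).
- s² = 0.042 × 0.88/600 = 0.0000616 and t² = 0.12 × 0.042 = 0.00504, taking 0.042 as the total variance.
- The brackets are 405 − 285 = 120 and 2025 + 4050 − 2850 − 2565 = 660.
- Var = 9 × 0.0000616 × 0.0504616 / 3.3338 = 0.00000839, so SE = 0.00290.
- z = 0.0084/0.00290 = 2.90, and power = Φ(2.90 − 1.96), about 82.6%.

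This reproduces the stated 83%, so the layout is right: 45 control and 45 MiM+ ICU-months.

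**Inputs for the patient-level check.**

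- Patients per ICU-month: 11200/9/12, about 104 (Study setting).
- ICC of the secondary outcomes: not stated. I assume 0.001 to 0.12, where 0.12 is the primary-outcome value.
- No effect and no time trend.

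**Formula.** For an outcome with total variance 1 and ICC ρ, each ICU's own level enters the pooled MiM+ minus control difference with weight (MiM+ months − control months)/45. The nine differences are 8, 6, 4, 2, 0, −2, −4, −6 and −8. Their squares sum to 240, and 240/2025 = 0.1185.

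- True variance = 0.1185ρ + (1 − ρ) × 2/(45 × 104).
- Variance assumed by the simple test = 2/4680 = 0.000427.
- Type I error = 2[1 − Φ(1.96 × √(assumed/true))].

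At ρ = 0.01 the true variance is 0.001185 + 0.000423 = 0.001608. The standard error is too small by a factor of 1.94, and the error is 31%. At ρ = 0.12 the true variance is 0.01422 + 0.00038 = 0.0146, the factor is about 5.8, and the error is 74%.

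| Assumed ICC | Type I error of a nominal 5% test |
|---|---|
| 0.001 | 8% |
| 0.005 | 20% |
| 0.01 | 31% |
| 0.02 | 44% |
| 0.05 | 61% |
| 0.12 | 74% |

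**Robustness.**

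- Simulation gave 30% (t-test), 32% (chi-squared) and 30% (Mann-Whitney) at ICC 0.01, and 73% to 75% for the three tests at 0.12.
- Unequal ICU sizes, chosen to match the stated total, median and quartiles, gave 31% to 32% (t-test and chi-squared) at ICC 0.01 and 75% to 76% at 0.12.
- Dropping each ICU's pilot month gave 34% (t-test) at ICC 0.01 and 76% at 0.12.
- With half as many patients (52 per ICU-month), the formula gives 20% at ICC 0.01 and 64% at 0.12.

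**Calendar time alone.** With no clustering, a drift of 0.05 standard deviations over the ten months gave 18% error in simulation, and 0.10 gave 51%. With neither clustering nor drift it was 5%. The drift sizes are also assumptions.

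**Override rate.** These figures do not describe it. According to the Study setting and Intervention sections, five ICUs already use MiM and four do not. The four can log no alerts, and so no overrides, before MiM+. A pooled test would compare control alerts from at most five ICUs with MiM+ alerts from nine.

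**The case against.** The strongest objection is about the text. The two testing sentences directly follow one on descriptive statistics, and the effect of the intervention is first mentioned after them, together with clustering and time. They may be meant only for patient or ICU characteristics. The article is also a condensed protocol, and models for secondary outcomes are commonly left to an analysis plan that is not shown. The Discussion shows that the authors know about within-cluster similarity and temporal confounding.

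Part of this stands. The document does not expressly assign the simple tests to the secondary outcomes, so the inflation is conditional on that use. The mere absence of named secondary models would not be a finding. What remains is that the text positively names unadjusted tests for comparing variables, sets no limit on their use, and restricts the clustered model to one measure. The benign reading does not fully rescue it either. If patient characteristics were compared between conditions with these tests, ordinary differences between ICUs would often appear as significant imbalance.

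A reader might infer two stronger things that the documents do not support. One is that false-positive rates of about 30% to 75% are a settled property of the plan. They hold only for ICCs of roughly 0.01 to 0.12, and no ICC is given for any secondary outcome. The other is that most significant secondary results would be artefacts. That depends on how many outcomes truly change and with what power, whereas the calculation covers only the case of no effect.

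**Conclusion.** The point holds in conditional form. As worded, the plan allows tests that ignore ICU and month to be used for control-versus-MiM+ comparisons of patient-level secondary outcomes, and names nothing else for them. In that use, the true error of a nominal 5% test would run from about 8% to 74% over ICCs of 0.001 to 0.12. This assumes about 104 patients per ICU-month, no effect and no time trend; a drift over the ten months can inflate the error even without clustering. Some secondary outcomes are per-patient forms of the primary outcome, so appreciable clustering is plausible, but its size is not documented. For the override rate, a pooled comparison is unsound whatever the ICC, because the two conditions draw on different sets of ICUs. The primary analysis by generalized estimating equations is not affected.

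**What to change.** Reword the Statistical analysis section in three places.

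1. Say that the t-test, Mann-Whitney, chi-squared and Fisher tests serve only description that is not a comparison of trial conditions, or drop them.
2. Say that every secondary outcome compared between control and MiM+ is analysed with a generalized linear model that accounts for ICU clustering (for example by generalized estimating equations) and adjusts for month. The link should suit the outcome: log for counts, logit for proportions, and a log-transformed or gamma model for length of stay.
3. Compare override rates before and after MiM+ only within the five ICUs that have control-period alerts. Report the other four ICUs' MiM+ override rates separately, without a before-and-after contrast.

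The cost is a few lines of text and a few more models, with no change to data collection or conduct. Confidence intervals will generally be wider, as they should be, and the override comparison will rest on five ICUs.

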**Methods:**

To define the clinically relevant pDDIs, we will follow a rigorous two-step Delphi procedure in which a national expert panel will assess which pDDIs are perceived clinically relevant for the Dutch ICU setting. The intervention is the CDSS that generates alerts based on the clinically relevant pDDIs. The intervention will be evaluated in a stepped-wedge trial. A total of 12 Dutch adult ICUs using the same patient data management system, in which the CDSS will operate, were invited to participate in the trial. Of the 12 ICUs, 9 agreed to participate and will be enrolled in the trial. Our primary outcome measure is the incidence of clinically relevant pDDIs per 1000 medication administrations.

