### Intervention

Our intervention consists of a version of the MiM that will only provide alerts for pDDIs considered clinically relevant in the ICU, according to our Delphi procedure. pDDI alerts considered not clinically relevant for the ICU will be turned off. This MiM version tailored to the ICU setting will be called MiM+. Our hypothesis is that alert fatigue can be reduced by MIM+, as the set of pDDIs for which alerts are provided at the point of prescribing, will be restricted and more specific for the ICU setting.

In the four participating ICUs that do not use the current MIM CDSS for pDDIs, the MiM+ software will be installed. Duplicate order alerts will not be shown in these four ICUs.

In the five ICUs that already use MiM as CDSS for pDDIs, MiM+ will start operating in these ICUs during the intervention phase. However, pDDI alerts not assessed during our Delphi procedure and for which an ICU gets alerts according to its current alert level setting, will not be changed. Furthermore, other types of alerts such as duplicate order alerts will also not be changed by our intervention. In short, the ICUs with a MiM CDSS will experience change in the alerts that were assessed in the Delphi rounds, in the sense that alerts for the pDDIs deemed irrelevant will be suppressed. All participating ICUs will receive an on-site training for the prescribing physicians about MiM+ given by a researcher involved in this study.

Apart from this intervention, all participating ICUs will receive two performance feedback rapports before MiM+ implementation. In these reports, results of a retrospective analysis of medication administration data on the occurrence of pDDIs will be included. The results will include pDDI occurrence over one year for the specific ICU, benchmarked against the other participating ICUs.

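### The only stepped-wedge effect model is stated for all pDDIs per 1000 administrations, while the primary outcome and the power calculation concern clinically relevant pDDIs

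*Protocol article*

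**What the plan says.** In the protocol article, the Statistical analysis section states its target as follows: "To assess the effect of tailoring pDDI alerts to the ICU setting on the number of pDDIs per 1000 medication administrations". The model comes next: "A generalized linear model will be fitted with correction for clustering via generalized estimating equations". No other model for the intervention effect is given.

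The outcome is described differently elsewhere:

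- Abstract, Methods: "Our primary outcome measure is the incidence of clinically relevant pDDIs per 1000 medication administrations".
- Study outcomes: "The primary outcome of this study is the incidence of clinically relevant pDDIs per 1000 medication administrations".
- Data collection: "These data are necessary to assess the primary outcome: the occurrence of clinically relevant pDDIs per 1000 medication administrations".
- Sample size: the anticipated improvement is "the overall difference in the number of clinically relevant pDDIs per 1000 medication administrations before and after the MiM+ implementation", with 42.0 per 1000 before and 33.6 after.

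Table 1 has one row for a pDDI and another for a clinically relevant pDDI, the latter tied to the Delphi result. The secondary outcomes keep the two apart: "These are the number of pDDIs per patient, the number of clinically relevant pDDIs per patient", followed by the proportions of patients with at least one of each. All pDDIs therefore appear per patient or as a proportion of patients, never per 1000 administrations.

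**The concern.** The quantity named in the analysis sentence matches neither the primary outcome nor any listed secondary outcome. If the sentence is followed as written, the main test is run on a rate that the protocol neither declares nor powers.

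The difference has substance because of what the intervention does. According to the Intervention section, all pDDIs fall into three groups:

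- Pairs judged relevant in the Delphi procedure, for which MiM+ gives alerts.
- Pairs judged irrelevant. In the five ICUs already using MiM, "alerts for the pDDIs deemed irrelevant will be suppressed".
- Pairs not assessed in the Delphi procedure, for which existing alerts stay as they are.

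The protocol describes a route by which MiM+ lowers the first group. It describes none for the other two. Counting all three together would add events that are not expected to fall, which shrinks the relative effect and adds variance.

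**Working it through.** **Step 1. Inputs, all from Sample size.** 9 clusters, 10 periods, one cluster crossing at each of 9 steps, 600 administrations per cluster per period, rates 42.0 and 33.6 per 1000, ICC 0.12, two-sided Wald Z-test at 0.05, Poisson counts, stated power 83%.

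**Step 2. Reproduce the stated power.** I used the Hussey–Hughes variance with fixed period effects:

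Var = I·σ²·(σ² + T·τ²) / [(I·U − W)·σ² + (U² + I·T·U − T·W − I·V)·τ²]

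Here I = 9 and T = 10. U is the number of intervention cells (45). W and V are the sums of squared column and row totals (285 each). So I·U − W = 405 − 285 = 120, and the second bracket is 2025 + 4050 − 2850 − 2565 = 660.

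Taking the Poisson control rate as the total variance:

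- τ² = 0.12 × 0.042 = 0.00504
- σ² = 0.88 × 0.042 / 600 = 0.0000616
- Var = 9 × 0.0000616 × 0.0504616 / (0.007392 + 3.3264) = 8.39 × 10⁻⁶, so SE = 2.90 per 1000
- Z = 8.4 / 2.90 = 2.90, and power = Φ(2.90 − 1.96) = 82.6%

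This agrees with the stated 83%, which therefore belongs to clinically relevant pDDIs only. The variance convention matters a little: with the full Poisson rate as within-cluster variance, power is 77.6% at the control rate and 81.8% at the mean rate.

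**Step 3. Apply the same model to all pDDIs.** The article does not give the rate R of non-relevant pDDIs per 1000. I assume R from 21 to 126, no change in these pDDIs under MiM+, and the same ICC. The absolute fall stays at 8.4 per 1000, the relative change is −8.4 / (42 + R), and the variance scales with 42 + R.

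| Assumed R per 1000 | All-pDDI rate per 1000 | Relative change | SE per 1000 | Power |
|---|---|---|---|---|
| 0 (relevant only) | 42 | −20% | 2.90 | 82.6% |
| 21 | 63 | −13.3% | 3.55 | 66% |
| 42 | 84 | −10% | 4.10 | 54% |
| 84 | 126 | −6.7% | 5.02 | 39% |
| 126 | 168 | −5% | 5.79 | 30% |

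Under the other convention (full Poisson control rate within clusters), the four diluted rows give 60%, 49%, 35% and 27%, so the pattern does not depend on that choice.

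**Step 4. Could the sign reverse?** Cancelling a fall of 8.4 per 1000 requires non-relevant pDDIs to rise by 8.4 per 1000 on average over all nine ICUs. Alerts are suppressed only in the five ICUs that already use MiM. Suppose, generously, that every non-relevant pDDI in those five rises by 10%, with equal ICU weights and equal baseline rates. The average rise is then 10% × 5/9 = 5.56% of R:

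- R = 42: (2.33 − 8.4) / 84 = −7.2%
- R = 84: (4.67 − 8.4) / 126 = −3.0%
- R = 126: (7.0 − 8.4) / 168 = −0.8%

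The effect shrinks further but does not reach zero.

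**The case against.** The strongest reply is that this is a dropped qualifier and nothing more. The primary outcome is fixed consistently in the abstract, Study outcomes, Data collection and Sample size. The Background ends its statement of aim with the clinically relevant pDDIs. The analysis sentence does not call its quantity primary. The only pDDI count that the article lists per 1000 administrations is the primary outcome, so the shared denominator points to that outcome being meant. The article also shortens the term elsewhere: Study outcomes moves from appropriately handled clinically relevant pDDIs to plain pDDIs within one paragraph, and the Discussion refers simply to counting pDDIs. All of this stands, and it makes a slip the likelier explanation.

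It does not make the sentence correct. Table 1 and the secondary outcomes use the two terms as different measures, and the detection algorithm in Data collection yields both, so either rate could be computed from the same data.

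Two stronger readings are tempting, and the documents support neither. A reader might infer that the analysis could reverse the effect, because alerts are switched off for some pairs. Suppression is confined to Delphi-assessed pairs in five of nine ICUs, the article gives no expected rise, and the 10% scenario in the working stays below zero. A reader might also infer that unblinded investigators are free to choose between two primary outcomes. One unqualified sentence does not declare a second primary outcome, and presenting an all-pDDI rate as primary would contradict four other sections.

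**Conclusion.** The contradiction is real and needs correcting: the sentence that introduces the only effect model names a quantity that is neither the primary outcome nor any listed outcome. Its practical consequence is conditional. Dilution arises only if the sentence is followed literally and non-relevant pDDIs do not fall in proportion to the relevant ones. On those terms the planned 20% reduction would appear as about 13% to 5%, with power of about 66% to 30% instead of about 83%. These figures rest on an assumed 21 to 126 unchanged non-relevant pDDIs per 1000 and on carrying the ICC of 0.12 over to all pDDIs. The article supplies neither the non-relevant rate nor an ICC for all pDDIs, so the range illustrates the stake and does not estimate it.

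**What to change.** In the Statistical analysis section, insert *clinically relevant* before pDDIs in the sentence that introduces the model, and state that this model is the primary analysis. Label any analysis of all pDDIs as secondary. If an all-pDDI rate per 1000 administrations is wanted, add it to the listed secondary outcomes. The cost is a sentence or two of text. No extra data, design change or new power calculation is needed, because the existing calculation already refers to the clinically relevant rate.
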